### Study rationale

Early work in mouse models demonstrated that CTLA4-Ig could inhibit the memory B cell response, collapse ongoing GC B cell reactions and stop the rise in alloantibody following HT^28^. The addition of bortezomib to a continuous CTLA4-Ig regimen, but not bortezomib alone, led to sustained alloantibody suppression which mirrored the clinical response in a small cohort of renal transplant recipients^25^. The studies described thus far highlight that plasma cell directed therapies as part of desensitization regimens are limited by i) inadequate response, particularly in very highly sensitized candidates, ii) antibody rebound/PI resistance and iii) their side effect profile^13^. Rigorous non-human primate studies have shown that desensitization using proteosome inhibition (PI) and costimulatory blockade with Belatacept (BELA) as a ‘dual targeting approach’ reduces BMPCs, disorganizes GC responses, reduces DSA levels and prolongs allograft survival^29^, ^30^.

### Single institutional review board approval

WashU serves as the single institutional review board (sIRB) for the study. All participating sites have chosen to execute a reliance agreement with the WashU IRB for primary review of the protocol. Site-specific consent form modifications were incorporated as needed, such as language surrounding institutional requirements for HIPAA, and age of assent which may differ between sites. This clinical study is being conducted using good clinical practice (GCP), as delineated in Guidance for Industry: E6 Good Clinical Practice Consolidated Guidance 1, and according to the criteria specified in this study protocol.

### Known and potential risks

Risks associated with BELA: In the BENEFIT trial, a higher incidence of posttransplant lymphoproliferative disease (PTLD) was observed in BELA treated renal transplant recipients who were naïve for prior Epstein Barr virus (EBV) infection at time of transplant^31^. As such, we will exclude patients who are EBV seronegative. There is emerging evidence of BELA associated risks of greater CMV morbidity^32^.

Risks associated with CFZ: New onset or worsening of pre-existing cardiac failure, acute renal failure and pulmonary toxicity have been reported. Adverse reactions could include anemia, diarrhea, hypertension, fatigue, thrombocytopenia, peripheral neuropathy and dyspnea.

### Study population

Inclusion criteria: Patients between 10 and 24 years old, who are being considered for HT and found to be highly sensitized with class I and or class II cPRA ≥ 50% utilizing the MFI threshold of 4000 (cPRA_MFI>4000_ ≥ 50%) will be considered for this desensitization strategy.

Exclusion criteria: EBV seronegative; HIV+; history of hematologic malignancy; inability to give a written informed consent or comply with study protocol.

### Number of subjects and sample size justification

A cohort of 30 patients across the 6 clinical sites during the 4-year study period is fixed by the limited population of patients meeting eligibility criteria for the study. This study is preliminary and results from the current work will be used to inform reasonable effect sizes when calculating power and sample sizes for a larger-scale study. With a cohort of 30 patients, we will have 80% power to detect moderate standardized effect sizes of Cohen’s d = 0.53 for analyses using paired t-tests and Cohen’s d=0.55 for analyses using Wilcoxon Signed Rank tests (Aim 1). We will also have 80% power to detect a large Chi-square effect size of W=0.51 (Aim 3).

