**Methods:**

This prospective, observational study will include about 30 patients from 6 pediatric clinical sites, an HLA core and a mechanistic core lab. Patients aged 10–24 years, highly sensitized with class I and/or class II cPRA ≥ 50% (MFI > 4000), will be included. Exclusion criteria: EBV seronegative, HIV+, and a history of hematologic malignancy. Secondary endpoints include mechanistic studies on how desensitization affects cellular subsets producing HLA Abs, whether reductions in antibody strength persist until transplant, and post-transplant outcomes such as antibody mediated rejection and graft survival.

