#### Primary aim

Study the efficacy and effectiveness of our proposed combined protocol with CFZ and BELA. We will investigate whether each cycle of desensitization is effective at.

i) reducing antibody strength as measured by MFI and titers and.

ii) lowering the calculated panel reactive antibody (cPRA).

We hypothesize that this protocol will lead to a meaningful decrease in antibody strength, with stepwise dilution of serum demonstrating gradual elimination or decrease in MFI such that the corresponding antigens would no longer be considered unacceptable. This would lower the cPRA, thereby allowing the use of a greater donor population. We will also determine whether the reduction in antibody strength is maintained with BELA between the last cycle and time of transplant. Reduction in DSA at the time of crossmatch will be studied to establish the functional relevance of our strategy. Sensitizing events defined per CTOT criteria^3^, as well as clinical events associated with the use of the proposed protocol will be monitored.

#### Secondary aim 1

Determine how desensitization impacts cellular subsets responsible for circulating anti-HLA antibodies. Using a series of state-of-the art techniques, we will combine global approaches (multiparameter flow, transcriptomics) with studies to delineate antigen specific responses (allo and viral) together establishing how desensitization shapes the B- and T-cell compartment and determine whether the response is sustained under BELA.

#### Secondary aim 2

Assess waitlist mortality and post-transplant outcomes using the Pediatric Heart Transplant Society (PHTS) database. We hypothesize that mortality before and after transplant will be comparable to overall PHTS outcomes^5^, both with and without positive crossmatch. Crossmatch (XM) status at the time of transplant will be recorded for each patient, and patients will be followed for at least one year after transplant to assess for antibody mediated rejection (AMR), ISHLT grade acute cellular rejection ≥2R (ACR), cardiovascular mortality, or need for retransplantation. While the primary analysis will focus on the first post-transplant year to align with available PHTS data, we anticipate extending this work in the future to evaluate longer term outcomes as data maturity allows.

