### Antibody evaluation

We will collect samples pre and post each cycle to assess for any change in class I and class II anti-HLA abs (MFIs, titer and cPRA). They will also be collected at two-week intervals during the maintenance phase. Serum samples will be sent to, logged, processed, and stored at the HLA core ([name]). Serum samples will be aliquoted in multiple vials to minimize the need of freezing and thawing. Per manufacturer’s instructions, LS1A/LS2A tests will be performed for single-antigen bead (SAB) analysis on the LuminexTM system (One Lambda Thermo Fisher, Canoga Park, CA). The reactions of a given anti-HLA specificity will be expressed as MFI. The drawbacks of using cPRA based on neat MFI values is that i) it only provides a semi-quantitative measure of alloantibody that is impacted by inherent assay limitation and laboratory variability and ii) partial therapeutic effects can be missed because reduction in antibody quantity without completely removing it does not translate to a change in cPRA. One way to overcome these weaknesses is by performing serum dilutions to determine antibody titer and establish the cPRA at various titers. Stepwise dilution of the serum will gradually eliminate antibody positivity and thus decrease the cPRA because the corresponding antigens would no longer be considered unacceptable^7^. We expect that this approach will help stratify patients prior to inclusion in studies and assist in discerning partial therapeutic effects. Titration of serum pre-testing will be performed (1:4, 1:16, 1:64 dilutions) and re-tested for antibody specificity on SAB analysis. We will evaluate the cPRA at different time points and at different dilutions to determine significant changes. A meaningful response following the cycles of treatment will be defined in two ways:i)cPRA < 50% using an MFI threshold ≥ 4000 based on previous data^15^ orii)50% reduction in MFI and a 2-log reduction in titer as recommended by the Sensitization in Transplantation: Assessment of Risk (STAR) 2022 Working Group^6^.

Antibody evaluation done at the core lab will not be used for clinical decision making at the study sites; those decisions will be made based on antibody evaluations from the HLA laboratories of the individual sites, per their routine practice.

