### Statistical and analytical plan

To evaluate the effect of each individual cycle of CFZ+BELA on cPRA, we will fit a linear mixed model with the patient treated as a random effect to control for repeated measures from the same patient. Continuous data (MFI) will be evaluated by mean MFI for class I and class II antibodies respectively with significance determined using student’s T-test. Net MFI reduction will be calculated as: (pre-treatment mean MFI – post treatment mean MFI) / pre-treatment mean MFI. Descriptive statistics in the form of means and standard deviations or medians and inter-quartile ranges will be calculated before and after desensitization cycles for all antibody titers of interest and cPRA. Multivariable analyses of covariance will examine changes in antibody titers and cPRA after controlling for a limited number of clinically important covariates. Paired t-tests or Wilcoxon Signed Rank tests will also be used to examine whether levels of antibody titers and cPRA remain constant between the last desensitization cycle and time of transplant, and to assess reductions in DSA.

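### The 80% power stated for 30 patients fits the pre/post-cycle comparisons but does not carry over to the last-cycle-to-transplant and DSA tests, which include only patients who reach transplant or crossmatch

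*Protocol article*

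**What the plan says.** The section on number of subjects explains that the size is set by feasibility: "A cohort of 30 patients across the 6 clinical sites during the 4-year study period is fixed by the limited population" of eligible patients. It calls the study preliminary and then states: "With a cohort of 30 patients, we will have 80% power to detect moderate standardized effect sizes". The effects are "d = 0.53 for analyses using paired t-tests" and "d=0.55 for analyses using Wilcoxon Signed Rank tests (Aim 1"), plus W = 0.51 for a chi-square test assigned to an Aim 3. It states no significance level, no degrees of freedom and no allowance for patients who are not transplanted.

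The statistical and analytical plan gives a linear mixed model for the effect of each cycle on cPRA, Student's t-test for mean MFI by class, and analysis of covariance for adjusted changes in titer and cPRA. Paired t-tests or Wilcoxon signed rank tests appear by name once: to examine whether titers and cPRA "remain constant between the last desensitization cycle and time of transplant, and to assess reductions in DSA".

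The primary aim places the DSA analysis at the time of crossmatch. Secondary aim 2 covers waitlist mortality as well as post-transplant outcomes; for the latter, "patients will be followed for at least one year after transplant to assess for antibody mediated rejection (AMR") and other events. The study labels one primary aim and secondary aims 1 and 2. No Aim 3 is listed.

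**The concern.** The power statement is tied to named tests and to 30 patients. The plan uses those named tests for questions that a patient can enter only after reaching transplant or a donor crossmatch. A study that lists waitlist mortality as an outcome does not expect all 30 to get there. For these questions the stated power is therefore too high, by an amount that depends on how many are transplanted.

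The durability question makes this matter more than usual. The plan asks whether levels stay constant, so a non-significant test is the result a reader would welcome. Low power makes that result more likely whatever the truth. Durable suppression under belatacept is central to the study's rationale, and a real rebound could be missed and then reported as maintained response.

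**Working it through.** **Inputs from the protocol article.** n = 30; power 80%; d = 0.53 (paired t); d = 0.55 (Wilcoxon); W = 0.51 (chi-square).

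**Assumptions, since the article gives none.** Two-sided alpha of 0.05; 1 degree of freedom for the chi-square; 27, 24, 20 or 15 of 30 transplanted (90%, 80%, 67%, 50%).

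**Formulas.**
- Paired t: noncentral t with n − 1 df and noncentrality d√n. Power is the probability of falling beyond ±t(0.975; n − 1).
- Wilcoxon: the same with n replaced by n × 3/π, the asymptotic relative efficiency under normality.
- Chi-square: noncentral chi-square, 1 df, noncentrality nW².

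**Step 1: reproduce the plan's figures at n = 30.**
- Paired t: 0.53 × √30 = 2.903, critical value 2.045; power 80.1%, detectable d 0.529.
- Wilcoxon: 30 × 3/π = 28.65 and 0.55 × √28.65 = 2.944; power 81.1%, detectable d 0.543. A simulation with normal data also gave 81.1%.
- Chi-square: 30 × 0.51² = 7.803; power 79.8%, detectable W 0.511.

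All three agree with the stated 80%. Variants that do not fit: a one-sided t-test (88.3%), and chi-square with 2 df (70.6%) or 3 df (64.2%).

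**Step 2: who can contribute.**

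| Analysis | Requires | Patients available |
|---|---|---|
| MFI, titer, cPRA before and after a cycle | Samples around a cycle | Up to 30 |
| Waitlist mortality | Listing | Whole cohort |
| Titer and cPRA, last cycle to transplant | A time-of-transplant value | Transplanted only |
| DSA reduction | A donor and crossmatch | Those reaching crossmatch |
| Rejection, retransplantation, first-year outcomes | A transplant | Transplanted only |

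**Step 3: recompute for the assumed numbers.** For example, at n = 20 the noncentrality is 0.53 × √20 = 2.370 against a critical value of 2.093, giving 61%.

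| n | Power, paired t, d = 0.53 | Power, Wilcoxon, d = 0.55 | 80%-detectable d, paired t | 80%-detectable d, Wilcoxon |
|---|---|---|---|---|
| 30 | 80% | 81% | 0.53 | 0.54 |
| 27 | 76% | 77% | 0.56 | 0.57 |
| 24 | 70% | 71% | 0.60 | 0.61 |
| 20 | 61% | 62% | 0.66 | 0.68 |
| 15 | 48% | 49% | 0.78 | 0.80 |

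If W = 0.51 refers to a post-transplant outcome, the detectable W becomes 0.54, 0.57, 0.63 and 0.72 for n = 27, 24, 20 and 15.

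**Step 4: what a non-significant durability test would mean.** At n = 15 a true change of d = 0.53 is missed with probability 1 − 0.48 = 0.52. The 95% confidence interval for the mean change extends t(0.975; n − 1)/√n standard deviations either side: 2.045/√30 = 0.37 at n = 30 and 2.145/√15 = 0.55 at n = 15. An interval that wide can contain no change and a moderate rebound together.

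**The case against.** The strongest reply is that nothing is miscalculated. The figures are explicitly conditional on 30 patients and are attached to Aim 1, whose core is the change around each cycle. The statistical plan introduces the transplant-dependent tests as an additional use, and the pre/post MFI t-test is not restricted to transplanted patients. The study is described as preliminary, its size is fixed, and the limitations section concedes a modest sample.

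Much of this stands. A reader might infer that every paired analysis is confined to transplanted patients and that the stated power applies nowhere. The article does not support that: comparisons around a cycle are paired by nature and can use all 30. What remains is that the power sentence covers all analyses using these tests, and the only ones for which the plan names them depend on transplant or crossmatch. A general remark about a modest sample does not correct a specific power figure.

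Three further inferences go too far.
- **Multiplicity.** The plan does speak of significance across time points and dilutions: "We will evaluate the cPRA at different time points and at different dilutions to determine significant changes". But the power is per test, no family-wise control is promised, and any adjustment or choice of a single primary endpoint may sit in the SAP, which is not shown.
- **Chi-square.** W = 0.51 cannot be called wrong for its population, because that population is not identified. Secondary aim 2 includes waitlist mortality, which uses the whole cohort.
- **Endpoint level.** The abstract lists "whether reductions in antibody strength persist until transplant" among secondary endpoints, while the study design discusses it under the primary aim. This is mainly labelling and does not affect the power calculation.

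**Conclusion.** The point holds in limited form. The 80% power is correct at n = 30 for one two-sided 5% test and suits the pre/post-cycle comparisons. It does not hold for the durability and DSA tests unless every patient reaches transplant or crossmatch, and the plan's own outcomes imply that some will not.

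The size of the loss cannot be derived from the article. Over the assumed range of 27 down to 15 transplanted, paired-t power at d = 0.53 falls from about 76% to 48%, and the detectable d rises from 0.56 to 0.78. The low end matters; at 27 the loss is small. The figures further assume that every transplanted patient has both measurements and, for the Wilcoxon test, roughly normal differences.

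The Aim 3 label matches no listed aim, so the population behind W = 0.51 cannot be determined. The sample size itself is not in question.

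**What to change.** In the section on number of subjects and sample size:

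1. Limit the 80% statement (d = 0.53 and 0.55) to pre/post-cycle comparisons in all 30 patients, and state the two-sided 5% level if that is what was used.
2. For durability and DSA reduction, add a short table of detectable effects by assumed number transplanted. For 27 / 24 / 20 / 15: d = 0.56 / 0.60 / 0.66 / 0.78 (paired t) and 0.57 / 0.61 / 0.68 / 0.80 (Wilcoxon). The investigators should replace the assumed counts with their own expected number.
3. Replace the Aim 3 label with the aim, outcome and population that W = 0.51 serves. If it is a post-transplant outcome, restate W for the number transplanted: 0.54 / 0.57 / 0.63 / 0.72.

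In the statistical and analytical plan, state that a non-significant last-cycle-to-transplant test is not evidence of constant levels, and report the mean change with its confidence interval and the number of patients contributing.

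The cost is a few sentences and one small table. No patients, visits or assays are added. The downside is that the stated figures look less favourable.

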### Rationale for why an IND is not needed

CFZ and BELA are two lawfully marketed drugs utilized for desensitization in medical practice, especially in patients who are highly sensitized. The intent in these scenarios is to treat the patient and attempt to increase the donor pool so that the patient can undergo heart transplantation. We aim to observe how these drugs impact the HLA antibodies, as determined by a core laboratory. This is not a clinical trial, and we do not intend to study a new indication, change the labeling or advertising of the drug. The study does not involve a route of administration, dose, patient population or other factor that significantly increases the risk (or decreases the acceptability of the risk) associated with the use of the drug products. The study will be conducted in compliance with the requirements for review by the IRB and with requirements for informed consent. The study is not intended to promote or commercialize the drug products. This approach complies with the FDA's "Guidance for Clinical Investigators, Sponsors and IRBs: Investigational New Drug Applications (INDs) – Determining Whether Human Research Studies Can be Conducted Without an IND.".

### Study regimen

The desensitization protocol is a combination of CFZ and BELA to be given every week for 4 weeks as part of one cycle (Figure 2). CFZ 20 mg/m^2^ IV on day 1, 27mg/m^2^ on day 2, and 36 mg/m^2^ on days 8, 9, 15, and 16. Patients will receive pre-medication with acetaminophen, diphenhydramine, methylprednisolone and ondansetron to minimize side effects. Patients will also be pre-hydrated with 500 ml normal saline prior to CFZ based on clinical status. BELA 10 mg/kg on days 1, 8, 15, and 28, and q28 days after first cycle; to be infused over 30 min using a 0.2-to-1.2-micron low protein binding filter. We anticipate that a number of patients will need multiple cycles in order to have sequential reduction in antibodies and to increase the likelihood of finding a donor. Once patients are deemed to be adequately desensitized (see Antibody evaluation), they will be maintained on monthly BELA (10 mg/kg) until the time of transplant. Following cycle 1, centers can choose to augment therapy (for example, with plasmapheresis) based on their established desensitization protocols and clinical judgment.

**Figure 2 fig0010:**
[figure not shown]
Desensitization Protocol using a combination of carfilzomib and belatacept. Human Leukocyte Antigen antibodies (HLA Abs); Peripheral Blood Mononuclear cells (PBMCs); Donor Specific Antibodies (DSA).

### Antibody evaluation

We will collect samples pre and post each cycle to assess for any change in class I and class II anti-HLA abs (MFIs, titer and cPRA). They will also be collected at two-week intervals during the maintenance phase. Serum samples will be sent to, logged, processed, and stored at the HLA core ([name]). Serum samples will be aliquoted in multiple vials to minimize the need of freezing and thawing. Per manufacturer’s instructions, LS1A/LS2A tests will be performed for single-antigen bead (SAB) analysis on the LuminexTM system (One Lambda Thermo Fisher, Canoga Park, CA). The reactions of a given anti-HLA specificity will be expressed as MFI. The drawbacks of using cPRA based on neat MFI values is that i) it only provides a semi-quantitative measure of alloantibody that is impacted by inherent assay limitation and laboratory variability and ii) partial therapeutic effects can be missed because reduction in antibody quantity without completely removing it does not translate to a change in cPRA. One way to overcome these weaknesses is by performing serum dilutions to determine antibody titer and establish the cPRA at various titers. Stepwise dilution of the serum will gradually eliminate antibody positivity and thus decrease the cPRA because the corresponding antigens would no longer be considered unacceptable^7^. We expect that this approach will help stratify patients prior to inclusion in studies and assist in discerning partial therapeutic effects. Titration of serum pre-testing will be performed (1:4, 1:16, 1:64 dilutions) and re-tested for antibody specificity on SAB analysis. We will evaluate the cPRA at different time points and at different dilutions to determine significant changes. A meaningful response following the cycles of treatment will be defined in two ways:i)cPRA < 50% using an MFI threshold ≥ 4000 based on previous data^15^ orii)50% reduction in MFI and a 2-log reduction in titer as recommended by the Sensitization in Transplantation: Assessment of Risk (STAR) 2022 Working Group^6^.

Antibody evaluation done at the core lab will not be used for clinical decision making at the study sites; those decisions will be made based on antibody evaluations from the HLA laboratories of the individual sites, per their routine practice.

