**Results:**

The study’s unique design harmonizes the use of a novel protocol across sites using a central IRB and is the first prospective, registry-based investigation in pediatric HT using the Pediatric Heart Transplant Society (PHTS) registry. The HLA core will measure antibody response through MFIs, titers, and cPRA, while the mechanistic core will use advanced investigations to support the trial's clinical endpoints.

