Despite these consequences, there is no standard-of-care approach to the sensitized PHT candidate. Importantly, desensitization is used less commonly than in the adult population, with only 25% of the patients in the above cohort receiving desensitization treatment. The implications of anti-HLA Abs on transplantation vary based on antibody strength as defined by mean fluorescence intensity (MFI) and antibody titer^6^. The presence of HLA Ab is determined by the Luminex single antigen bead (SAB) assay; we will define MFI in titer as a surrogate for antibody strength. Access to the donor pool is determined by entering unacceptable antigens based on center specific MFI cut off values into the online UNOS (United Network for Organ Sharing) calculator to determine the calculated panel-reactive antibodies (cPRA). The percent cPRA informs the clinical team as to the degree of sensitization, with a higher cPRA further limiting the donor pool (Figure 1). For example, a cPRA_MFI>4000_≥ 50% indicates that >50% of donors would be unacceptable because they have HLA antigens to which the HT candidate has HLA antibodies at levels > 4000 MFI**.** The change in cPRA on neat (undiluted) serum is an insensitive measure of effectiveness, and instead, the circulating HLA Ab should be risk stratified by performing serial dilutions with cPRA reduction calculated per antibody titer^7^, ^8^. This approach allows the clinical team to differentiate between HLA antigens that should be avoided from those that are potentially acceptable to cross. Dilutional analysis can act as a surrogate for complement-binding capacity (e.g., C1q positivity), and reduction in cPRA at lower titer thresholds has been associated with improved transplant outcomes.

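### Response criterion (i), cPRA below 50%, is a post-treatment state with no baseline condition, so a patient already below 50% at the core laboratory, or one who just crosses the line, counts as a responder

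*Protocol article*

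**What the plan says.** - **Entry** (Protocol article, Study population). Candidates for the regimen are patients aged 10 to 24 who are "found to be highly sensitized with class I and or class II cPRA ≥ 50% utilizing the MFI threshold of 4000". The section does not name the laboratory whose result decides this.
- **Response** (Antibody evaluation). Response is defined in two ways joined by 'or'. Criterion (i) is "cPRA < 50% using an MFI threshold ≥ 4000 based on previous data". Criterion (ii) is "50% reduction in MFI and a 2-log reduction in titer".
- **Laboratories.** The abstract (Results) states: "The HLA core will measure antibody response through MFIs, titers, and cPRA". Antibody evaluation adds: "Antibody evaluation done at the core lab will not be used for clinical decision making at the study sites". Sites act on results from their own HLA laboratories instead.
- **Sampling** (Antibody evaluation). Core samples are taken before and after each cycle and every two weeks in maintenance. The same section acknowledges that cPRA from neat MFI values is affected by assay limits and by variation between laboratories.
- **Analysis** (Statistical and analytical plan). cPRA goes into a linear mixed model by cycle, MFI is compared by t-test, and titers and cPRA are also examined by analysis of covariance. Study design describes no concurrent control group.

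**The concern.** Criterion (i) is the complement of the entry rule at the same MFI threshold. It asks only where the patient stands after treatment. It does not ask whether the patient stood above 50% beforehand in the laboratory that measures response, or by how much the value moved. Criterion (ii) does require a change. Because the two are joined by 'or', meeting (i) alone is enough.

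Two kinds of patient can then be classed as responders without a real drug effect:

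1. A patient treated on a site result of at least 50% whose core value was already below 50% before cycle 1.
2. A patient just above 50% whose next reading falls just below it, for example from 51% to 49%, through reading variation alone.

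Without a concurrent control, neither can be told apart from a treatment effect by counting responders. The sample size section says the results will inform effect sizes for a larger study, so an overstated response proportion could be carried forward if it were used for that.

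**Working it through.** **The plan's own figures.** No figure is given for the proportion of responders. The sample size section states 80% power with 30 patients for other analyses, and these reproduce: paired t-test at d = 0.53, 80.1% (two-sided alpha 0.05 assumed); Wilcoxon signed rank at d = 0.55, 81.1% (asymptotic relative efficiency 3/π); chi-square at W = 0.51, 79.8% (1 df assumed). They are not in dispute and do not bear on criterion (i).

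**Step 1: the rules side by side.**

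| | Entry | Criterion (i) | Criterion (ii) |
|---|---|---|---|
| Rule | cPRA ≥ 50%, class I and/or II, MFI 4000 | cPRA < 50%, MFI 4000 | falls in MFI and in titer |
| Needs a baseline value | not applicable | no | yes |
| Laboratory | not named; clinical decisions use the site | HLA core | HLA core |

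A patient with site cPRA of at least 50%, core pre-cycle-1 cPRA below 50% and an unchanged core value afterwards satisfies criterion (i) as printed. This needs no assumption about variance, only that the two laboratories can disagree, which the article accepts. How often it happens cannot be known from the document.

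**Step 2: one patient near the cut-off.** Inputs: observed baseline b and within-patient reading SD s. The document gives no SD; 3, 5 and 7 cPRA points are assumptions. With no true change, the chance that the next reading is below 50% is about Φ((50 − b)/(s√2)). Example: b = 55, s = 5 gives Φ(−5/7.07) = Φ(−0.71) = 24%.

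| Observed baseline | s = 3 | s = 5 | s = 7 |
|---|---|---|---|
| 52% | 32% | 39% | 42% |
| 55% | 12% | 24% | 31% |
| 60% | 1% | 8% | 16% |
| 70% | 0% | 0.2% | 2% |

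**Step 3: the cohort.** Simulation of 1,000,000 patients: true cPRA drawn from an assumed distribution, normal reading error, entry on one reading of at least 50%, one independent second reading, no treatment effect. Share with the second reading below 50%, and expected number of 30:

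| True cPRA | SD 3 | SD 5 | SD 10 | SD 15 |
|---|---|---|---|---|
| Uniform 70–100 | 0% (0) | 0% (0) | 0.3% (0.1) | 2.1% (0.6) |
| Uniform 50–100 | 1.7% (0.5) | 2.9% (0.9) | 6.2% (1.8) | 9.6% (2.9) |
| Uniform 0–100 | 3.4% (1.0) | 5.6% (1.7) | 11.2% (3.4) | 16.9% (5.1) |

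The same numbers apply if the second reading is the core pre-cycle-1 sample. They then give the share already below 50% at the core before any drug, provided the laboratories do not differ systematically.

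**Step 4: effect of anchoring.** Requiring core pre-cycle-1 cPRA of at least 50% removes the laboratory route by definition. It also acts as a second baseline reading. In the simulation at SD 5, false responders among patients with both baselines at or above 50% are 2.2% (uniform 50–100) and 3.0% (uniform 0–100). Expressed per 30 enrolled:

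- Uniform 50–100: 30 × 0.0220 × (1 − 0.0294) = 0.64, against 0.88 before.
- Uniform 0–100: 30 × 0.0297 × (1 − 0.0563) = 0.84, against 1.69 before.

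Some regression to the mean remains, which is why the change in points should be shown as well.

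**The case against.** The case for leaving the rule alone is substantial, and much of it stands.

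- **Continuous analyses.** No responder proportion is named as a primary or powered endpoint. The aims, the power statement for Aim 1 and the cPRA and MFI analyses are continuous and do not use this dichotomy. A reader might infer that the study's headline result is inflated; the document does not support that. Study regimen refers to this section when it describes moving to maintenance, but core results do not drive clinical decisions. This stands and limits the harm.
- **Class.** A reader might infer that a patient qualifying on class I could respond through a class II value that was never above 50%. That is a strained reading. The Introduction treats cPRA as a single donor-pool figure, and on that basis a patient with 85% in one class has at least 85% overall. What remains is that criterion (i) does not say which measure is used.
- **Laboratory.** The entry laboratory is not named, and the core takes a pre-cycle sample from which a same-laboratory baseline can be read. This stands: the switch is an inference. But criterion (i) does not use that baseline.
- **Single reading.** The text does not say that one reading is decisive; it schedules repeated samples. It simply states no confirmation rule.
- **Size.** High probabilities apply only close to 50%. Every SD and distribution is assumed.
- **Direction.** The remark "The change in cPRA on neat (undiluted) serum is an insensitive measure of effectiveness" concerns effects that are missed, so it is no evidence of spurious responses.
- **Condensed article.** The full protocol or analysis plan may add baseline and measure rules. It may, but the criterion is printed here as a fixed rule without them.

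The 50% threshold itself, described as based on earlier data, is a legitimate choice about donor access and is not challenged.

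**Conclusion.** The point holds in a limited form. As printed, criterion (i) can classify as a responder a patient whose core cPRA was below 50% before treatment, or who moved a point or two across the cut-off. Only the meaningful-response classification is affected.

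The size is uncertain and probably modest. With true cPRA uniform on 50 to 100 and SD 3 to 5, 0.5 to 0.9 of 30 patients would be false responders through reading variation; for a cohort at 70 to 100 the figure is practically zero. Larger counts, up to about 5 of 30, need an SD of 15 and a source population with many patients truly below 50%. All these figures rest on assumed SDs and distributions. The laboratory route needs no SD in principle, but its frequency is unknown and it assumes that entry follows the site result. The correction is worth making before response is classified because it costs almost nothing.

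**What to change.** Amend criterion (i) so that it counts only when the core-laboratory pre-cycle-1 cPRA was at least 50% on the same measure used for response. Fix that measure in advance: either the combined class I and II cPRA, or the cPRA of the qualifying class. Report each responder's change in core cPRA points beside the classification, and state how many patients had a core baseline below 50%. Those patients can still be assessed on criterion (ii) and stay in the continuous analyses.

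Confirmation of the value below 50% on the next scheduled sample may be shown as a sensitivity analysis. It should not be a requirement: a later sample mixes reading error with true antibody rebound, and patients transplanted soon after responding would have no confirming sample.

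Cost: endpoint wording only, with no extra visits or assays, because the core samples are already scheduled. A few patients will not be evaluable for criterion (i), and the proportion classed as responders may be slightly lower.
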